# **Reach Up early childhood parenting programme: Evaluation of Implementation and Benefits in Jamaica 2022**

Interviewer \_\_\_\_\_ Date \_\_\_\_\_ (dd/mm/yyyy)

Health Centre ID# \_\_\_\_\_ Subject ID# \_\_\_\_\_

1. Relationship of respondent to child
- |              |                 |
|--------------|-----------------|
| Mother       | _____           |
| Father       | _____           |
| Relative     | _____ (specify) |
| Non-Relative | _____           |

Who are the persons who live in the home with you (*indicate relationship to study child and get ages of **all children**; probe if persons **share food and sleep in the home**  $\geq 4$  nights/week*). Remember to include **respondent and child** in the list of persons.

---

2. Where does the mother live?

|                                  |                                   |
|----------------------------------|-----------------------------------|
| Mother lives with child          | _____ ( if yes, go to #4 ) |
| Same community/district as child | _____                             |
| Other community/district         | _____                             |
| Abroad                           | _____                             |
| Dead/unknown                     | _____                             |
| Other                            | _____                             |

3. *If mother, does not live in the home*, how often does child see his/her mother?

|                      |       |
|----------------------|-------|
| At least once/week   | _____ |
| At least once/month  | _____ |
| Less than once/month | _____ |
| Mother is deceased   | _____ |

4. Where does the father live?

|                                  |                                   |
|----------------------------------|-----------------------------------|
| Father lives with child          | _____ ( if yes, go to #6 ) |
| Same community/district as child | _____                             |
| Other community/district         | _____                             |
| Abroad                           | _____                             |
| Dead/unknown                     | _____                             |
| Other                            | _____                             |

5. *If father, does not live in home*, how often does child see his/her father?

|                      |       |
|----------------------|-------|
| At least once/week   | _____ |
| At least once/month  | _____ |
| Less than once/month | _____ |
| Father is deceased   | _____ |

**Caregiver's Age**

6. How old are you now? \_\_\_\_\_

**Caregiver's Education**

7. What was the highest grade you completed in school? \_\_\_\_\_

8. Did you complete any training after you left school? Yes \_\_\_\_\_ No \_\_\_\_\_

If yes, what

---

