### **Methods**

### *Selection of districts and sample*

Each Parish health team, led by the Medical Officer of Health, nominated the health district within the parish for the initial implementation phase (phase 1) and two nurses to be trained in the intervention. Initial impact and implementation evaluations were conducted in six parishes that began home visits before these were suspended in March 2020. Remote delivery was conducted in these parishes beginning in September 2020 and evaluated from July to October 2021. Feedback from health staff and families suggested the use of a blended intervention with home visits and phone calls. In this phase of the study the impact of the blended intervention on child development and parent practices will be evaluated.

The intervention will focus on children aged 6-24 months who meet at least one of the following criteria: families where the child or mother is registered with the Programme of Advancement through Health and Education (PATH) or the family resides in a low income setting. Children identified and whose mother provides consent to participate will be randomly assigned to either receive the intervention now or after 8 months (wait list group). Children assigned to the 'wait list' group will continue to receive usual care from the health centres.

Within each district the intervention will be implemented in 1-3 health centres that will comprise those supervised by the nurses trained. All community health aides (CHAs) assigned to these health centres will be trained to deliver the intervention, approximately 8 CHAs per district. So as to enable the CHAs to conduct the fortnightly intervention contacts (home visits and phone calls) together with their usual duties, each CHA will be assigned 8 families with 4 randomly assigned to intervention and 4 to the waitlist group. We therefore estimate 32 children in the intervention group per district and another 32 children per district in the wait list group, with a total of 416 per group across all parishes.

Mother-child pairs will be excluded if:

- Child is in Daycare or has no consistent caregiver
- The baby has major disability likely to affect development

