#### *Measurements*

Baseline - An interviewer administered questionnaire will be used to obtain information from the mother on the following (Appendix 1):

Maternal and family data: including mother's age and education, employment, family structure, standard of housing (crowding- person/room, type of toilet, water supply and household possessions). Information on father's age and presence in the home will also be obtained by maternal report. We will use a questionnaire previously used in Jamaica [14].

Attitudes on child development: mother's attitude concerning child development and her role in promoting child development, using a questionnaire previously used in Jamaica [14].

Parent Practices: questions from the Family Care Indicators questionnaire will be used to assess the activities the mother or principal caretaker does with the child [15]. The FCI has been modified for use in Jamaica and was used in the evaluation of the remote delivery intervention.

Maternal depressive symptoms: measures will be obtained by interview using the Brief Center for Epidemiological Studies-Depression (CES-D-10) scale[16]. The CES-D has been used previously in Jamaica [14].

Child: Date of birth and birth weight, current length and weight, will be obtained from the children's clinic records/ child passport.

End of intervention: The following sections of the questionnaire will be repeated – Attitudes on child development, parent practices and maternal depressive symptoms. Child development will be assessed with the Griffith Scales of Development [17] which have been used in several studies in Jamaica.

Checklist, observations

Evaluation Checklist: Supervisors will use an evaluation checklist to assess the quality of the visit or call. The quality of the visit or call includes assessment of the interaction between the home visitor, mother and child; the atmosphere of the visit and the preparation of the home visitor for the visit [18]. This checklist was developed previously in Jamaica and has also been used to monitor quality in other countries [18]. **(Appendix 1)**

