## **Data Analysis Plan:**

### **Impact evaluation**

Primary analyses for the impact evaluation will be by intention to treat. We will compare the groups on baseline measurements and will control for any measures which differ among the groups at endline in multivariate analyses of outcome.

Following the primary regression analyses we will investigate whether impact varies by maternal characteristics (education, depressive symptoms) or child characteristics (age on enrolment). We will also investigate the mechanism for impact to determine if change in parent practices mediates the impact on child outcomes.

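### When someone other than the mother answers the baseline form, her own age and schooling are recorded nowhere, although the plan relies on them; separately, a skip at item 9 bypasses items 12 and 13

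*Protocol*

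**What the plan says.** The Measurements section of the Protocol fixes the source of the baseline data: "An interviewer administered questionnaire will be used to obtain information from the mother on the following". The first block is described as "Maternal and family data: including mother's age and education, employment, family structure", and a later entry adds maternal depressive symptoms by the CES-D-10.

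The Data Analysis Plan (Impact evaluation) uses these variables in two ways. As moderators: "we will investigate whether impact varies by maternal characteristics (education, depressive symptoms". As possible covariates: the analysis "will control for any measures which differ among the groups" at baseline.

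The form in Appendix 1 opens with "1. Relationship of respondent to child" and offers mother, father, relative and non-relative. Items 2 and 3 provide for a mother who lives elsewhere, is abroad or has died. Items 6 to 13 are headed as the caregiver's and are put to the respondent; item 7, for example, reads "What was the highest grade you completed in school". The CES-D items are also put to the respondent.

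Within the employment block, a No at item 9 (current work) is sent to item 14. Items 12 and 13, on past work, stand under a cue that restricts them to people who are not working.

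**The concern.** The text and the form define different variables. The text speaks of the mother; the form records whoever answers. The two agree when the mother answers and part when she does not. For those children, a variable analysed as maternal education or maternal depressive symptoms would describe another adult, and the mother's own value could not be looked up later in the study data.

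At stake are the analyses of whether impact varies with maternal education or depressive symptoms, and any adjustment that uses the mother's age, education or work. A statistical analysis plan can redefine a variable, but it cannot supply data that the form never collected, so the point has to be settled in the form or in the definition of the moderators.

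The skip at item 9 is a separate data-capture error. It costs the past-work items for caregivers who are not working.

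**Working it through.** No formula in the Protocol bears on this point, so the check sets the plan beside the form item by item.

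| Variable | Planned as | Item in Appendix 1 | Mother answers | Someone else answers |
|---|---|---|---|---|
| Age | mother's | 6 | mother's | respondent's; mother's absent |
| Education | mother's; moderator | 7, 8 | mother's | respondent's; mother's absent |
| Employment | listed with the maternal data | 9 to 11 | mother's | respondent's; mother's absent |
| Depressive symptoms | maternal; moderator | CES-D | mother's | respondent's; mother's absent |
| First child or not | baseline item | 15 | mother's | mother's, because the item is worded for both cases |

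Item 15 shows that the form's authors foresaw a respondent who is not the mother. That wording was not carried to age, schooling or work. If the father answers, items 6 and 14 both record his age and no item records hers.

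**How many records.** The Selection section plans 416 children per group, so 2 × 416 = 832. If a share p of respondents are not mothers, 832 × p records are affected. The Protocol gives no p. Each percentage point is 832 × 0.01 = 8.32, about 8 records. Purely as assumptions:

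- p = 2%: about 17 records
- p = 5%: about 42
- p = 10%: about 83
- p = 20%: about 166

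**What is not touched.** The primary outcome is the child's developmental quotient, measured on the child with the Griffiths scales. The stated 178 per group rests on a difference of 3.6 points and an SD of 12. Neither uses a maternal variable.

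**Skip path, followed as printed.**

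- Item 9 = Yes: items 10 and 11, then 14, because the not-working cue before item 12 does not apply.
- Item 9 = No: straight to item 14.

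Items 12 and 13 are on neither path. Item 12 carries its own skip to item 14 for people who have never worked, which makes sense only if non-workers were meant to reach it.

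**The case against.** The strongest reply is that the mother is the planned respondent. The Measurements section says so, and enrolment depends on her: "Children identified and whose mother provides consent to participate will be randomly assigned". For every record in which she answers, items 6 to 11 and the CES-D are the maternal variables. A reader might infer that the form fails to capture maternal variables in general; the documents do not support that. The gap is confined to non-mother respondents. This part of the reply stands and sets the size of the point.

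Second, item 1 identifies the exceptions, so an analyst can set them to missing or treat them as caregiver values. That is true and prevents silent mislabelling if it is done, but it does not recover the mother's schooling.

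Third, the programme works through caregivers, and the Measurements section itself takes parent practices from either the mother or the main caretaker. Recording the person who gives the care may be what is wanted. If so, the wording of the moderators should change rather than the form, and the fix allows for this.

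Three stronger readings should be resisted.

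- A reader might infer that respondent identity is lost at endline, so that change in parent practices could compare two adults, because item 1 is not among the sections listed for repetition. The endline form is not shown, and a short list of content sections does not show that an identification item was left out.
- A reader might put a percentage on the dilution of the moderator effects. That needs both the share of non-mother respondents and the correlation between the two adults' values, and the Protocol gives neither.
- A reader might treat the skip error as a loss to the analysis. Past work enters no named analysis, current employment is still captured at items 9 to 11, and the printed cue may lead some interviewers to ask items 12 and 13 anyway.

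**Conclusion.** The point holds in a limited form. Appendix 1 admits a non-mother respondent but has no item for the mother's own age or schooling in that case. This conflicts with the Measurements section and with the maternal moderators in the Data Analysis Plan. It concerns an unstated and probably small share of the 832 planned children. It bears on secondary moderator analyses and on possible covariates, and it leaves the primary comparison and the sample size alone. The judgement that the share is small rests on the plan to interview the mother and on her consent, not on any figure in the Protocol.

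The item 9 skip is a definite but minor form error, on the reading that interviewers follow the printed instruction.

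**What to change.** Choose one of two routes, before baseline interviews if possible.

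1. **Add the items.** For non-mother respondents, ask the mother's age and highest grade, using the double wording already found in item 15. The current-work item could be worded in the same way. The CES-D is a self-report, so another adult's answers cannot stand in for the mother's; under this route the maternal score is missing for those records unless she is interviewed.
2. **Redefine the moderators.** In the Data Analysis Plan, call them primary-caregiver education and primary-caregiver depressive symptoms, align the Measurements section, and use item 1 to flag non-mother records. This is the route that remains if baseline data are already collected.

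Under either route, change the skip for No at item 9 from item 14 to item 12.

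The first route costs two form lines and a few seconds of interview time; the second costs a change of wording. The skip correction changes one number on the form.

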**Caregiver's Employment**

9. Do you currently work (i.e. work for someone or self-employed)?

Yes \_\_\_\_\_ No \_\_\_\_\_ (if no, go to #14)

(If on maternity leave code Yes)

10. Type of work? \_\_\_\_\_

11. Part time \_\_\_\_\_ Full time \_\_\_\_\_

If not working,

12. Have you ever worked? Yes \_\_\_\_\_ No \_\_\_\_\_ (if no, go to #14)

13. If yes, what was the last job you did? \_\_\_\_\_

**Father's age**

14. How old is father now? \_\_\_\_\_ D/K \_\_\_\_\_

**Child's Birth Information**

15. Is this your/the mother's first child? Yes \_\_\_\_\_ No \_\_\_\_\_

If No, how many other children do you/ does she have, before this child

\_\_\_\_\_  
(record all live births, and if a sibling has died)

Can I see the baby's child health passport? (**Child passport, pages 12-13**)

Child passport seen? Yes \_\_\_\_\_ No \_\_\_\_\_

16. Baby's sex Male \_\_\_\_\_ Female \_\_\_\_\_

17. Baby's Birth weight (kg) \_\_\_\_\_

18. Date of birth (day/month/year) \_\_\_\_\_

19. Where was he/she born? (record name of hospital/home delivery) \_\_\_\_\_

## Housing

20. What type of toilet do you have in your home?

|                      |   |            |   |
|----------------------|---|------------|---|
| Own inside flush     | 6 | Own pit    | 2 |
| Shared inside flush  | 5 | Shared pit | 1 |
| Own outside flush    | 4 | None       | 0 |
| Shared outside flush | 3 |            |   |

21. What is your household's main source for drinking water?

|                     |   |                                    |   |
|---------------------|---|------------------------------------|---|
| Own inside pipe     | 6 | Stored water not connected to home | 2 |
| Shared inside pipe  | 5 | Pipe outside of yard               | 1 |
| Own pipe in yard    | 4 | River or well/Other                | 0 |
| Shared pipe in yard | 3 |                                    |   |

## Crowding

22. No. of Children under 18 yrs. in the household \_\_\_\_\_ (refer to Ques#1)

23. No. of people over  $\geq 18$  yrs. (share food and sleep in the home  $\geq 4$  d/week)  
\_\_\_\_\_ (refer to Ques#1)

24. No. of rooms in household (total) \_\_\_\_\_  
(Do not count bathroom or kitchen unless can sit in kitchen and eat)  
(Count veranda if totally enclosed and someone can sleep there)

## Possessions

25. I'm going to read a list of items. Please say if there is one in your home in working condition.

|                                      | Yes | No |
|--------------------------------------|-----|----|
| Oil, Gas or electric stove           | 1   | 0  |
| Fridge                               | 1   | 0  |
| Washing machine                      | 1   | 0  |
| Living room set                      | 1   | 0  |
| Clothes Iron                         | 1   | 0  |
| Radio/Component Set                  | 1   | 0  |
| CD or DVD Player                     | 1   | 0  |
| TV                                   | 1   | 0  |
| Cable (TV)/Android Box/Ready TV      | 1   | 0  |
| Phone (Cell Phone/ Landline)         | 1   | 0  |
| Computer (desktop or laptop)         | 1   | 0  |
| Tablet                               | 1   | 0  |
| Bicycle ( not child's) | 1   | 0  |
| Motor bike                           | 1   | 0  |
| Motor car                            | 1   | 0  |

## Parenting Attitudes

Say, “Now I am going to ask you whether you agree or disagree with some statements about looking after young children. There are no right or wrong answers, we just want to know what you think or feel. You can also ask me to repeat the statements”.

1. Too much love and attention will spoil a child.  
agree completely    agree a little bit    disagree a little bit    disagree completely
2. A parent needs to spank or beat young children when they are rude or they will grow up to be bad.  
agree completely    agree a little bit    disagree a little bit    disagree completely
3. It is important that a busy mother spend plenty time talking with her little baby.  
agree completely    agree a little bit    disagree a little bit    disagree completely
4. It is important that parents look at picture books with children less than 2 years old.  
agree completely    agree a little bit    disagree a little bit    disagree completely
5. The best way to get a child to behave is to praise him when he is good  
agree completely    agree a little bit    disagree a little bit    disagree completely
6. It is important that a busy mother should spend plenty time playing with her young child.  
agree completely    agree a little bit    disagree a little bit    disagree completely
7. There is no need to give toys to children less than 1 year old.  
agree completely    agree a little bit    disagree a little bit    disagree completely
8. Children should not be given crayons until they are ready to learn to write  
agree completely    agree a little bit    disagree a little bit    disagree completely
9. Young children should not be held when they cry because they this will make them want to be held all the time  
agree completely    agree a little bit    disagree a little bit    disagree completely
10. How a parent behaves with her child when s/he is young affects how well s/he will learn in school.  
agree completely    agree a little bit    disagree a little bit    disagree completely

### CES- Short Depression Scale-Revised (Jamaica)

Say, “*This section is about how you might have been feeling or acting recently. I’m going to read some sentences which describe how persons sometimes feel. For each sentence, tell me if in the past week you felt or acted that way. Tell me if you felt that way **None of the time, A little of the time, some of the time or Most of the time.** Remember there are no right or wrong answers, only you can tell me how you feel*”.

| In the past week (from last __ till today)                                         | None
< 1 day | A little
1-2 d | Some
3-4 d | Most
5-7 d |
|-------------------------------------------------------------------------------------------|-----------------|-------------------|---------------|---------------|
| 1. You were bothered by things that usually don't bother you.                             | 0               | 1                 | 2             | 3             |
| 2. You found it hard to think properly or concentrate.                                    | 0               | 1                 | 2             | 3             |
| 3. You felt depressed.                                                                    | 0               | 1                 | 2             | 3             |
| 4. You felt everything was hard to do.                                                    | 0               | 1                 | 2             | 3             |
| 5. You felt good about the future.                                                        | 3               | 2                 | 1             | 0             |
| 6. You felt afraid.                                                                       | 0               | 1                 | 2             | 3             |
| 7. You did not sleep good.
You tossed and turned, had difficulty falling asleep | 0               | 1                 | 2             | 3             |
| 8. You felt happy.                                                                        | 3               | 2                 | 1             | 0             |
| 9. You felt lonely.                                                                       | 0               | 1                 | 2             | 3             |
| 10. You felt so tired you just sat around and did nothing                                 | 0               | 1                 | 2             | 3             |

## Parent Practices

Say, “We’re interested in knowing the kinds of things you and your children do in the home on a regular basis. I am going to ask some questions about activities you have been able to do with \_\_\_\_\_.”

- |                                                                                                                                                                                                                                                                                                     |     |    |
|-----------------------------------------------------------------------------------------------------------------------------------------------------------------------------------------------------------------------------------------------------------------------------------------------------|-----|----|
| 
1. Have you ever made any toys or things for (child’s name) to play with?
 If yes, how many? _____
 Please describe what you made.
 _____
 _____
                                                                                                        | Yes | No |
| 
2. Are there other toys (bought, gift, siblings’, made by others) in your home that (child’s name) can play with?
 If yes, how many toys? _____
 Please describe them for me.
 _____
 _____
                                                                    | Yes | No |
| 
3. In the past week, did you play with (child’s name) with a toy or other object?
 If yes, how many days? _____
 What did you do/play? _____
 _____
                                                                                           | Yes | No |
| 
4. In the past week, did you play any games or other activities with (child’s name) that did not need any toys (or tablet or phone) (e.g. peek-a-boo, clap hands, action songs, dance)?
 If yes, how many days? _____
 What did you do? _____
 _____
 | Yes | No |
| 
5. Are there any picture books or children’s books with pictures in your home for (child’s name) to look at?
 If yes, how many? _____
                                                                                                                                      | Yes | No |
| 
6. In the past week, did you read or look at pictures in a book (or tablet) with (child’s name)?
 If yes, how many days? _____
                                                                                                                                      | Yes | No |
| 
7. In the past week, did you tell (child’s name) any stories (made up or based on other story)?
 If yes, how many days? _____
                                                                                                                                       | Yes | No |

What stories? \_\_\_\_\_

8. In the past week, did you tell (*child's name*) the names of people or things in the home or outside? Yes No

If *yes*, how many days? \_\_\_\_\_

9. In the past week, did you sing with (*child's name*)? Yes No

If *yes*, how many days? \_\_\_\_\_

What songs did you sing? \_\_\_\_\_

10. In the past week, did you give (*child's name*) a crayon(s)/pencil and help him/her to scribble or draw? Yes No

If *yes*, how many days? \_\_\_\_\_

11. Parents are often very busy. When you are working in the house, like cleaning or washing, do you chat with (*child's name*) about what you are doing?

None of time      a little of the time      sometimes      most of the time

12. When (*child's name*) speaks or makes sounds do you respond or speak back to him/her?

None of time      a little of the time      sometimes      most of the time

13. Do you and (*child's name*) have conversations or chat together – like make sounds or speak back and forth to each other?

None of time      a little of the time      sometimes      most of the time

14. In the past week, did (*child's name*) do anything that pleased you or made you happy? Yes No

If *yes*, what did you do when this happened?

(do not read responses, circle all that apply)

Nothing      hugged/physical      praised child      give child something

15. When (*child's name*) behaves well or does something good how often do you praise him/her?

None of the time      a little of the time      sometimes      often/most of the time

